### The intervention: the primary care plus centre

The PC+ intervention is a cardiology PC+ centre in which cardiologists, supported by other health-care professionals, provide specialist consultations in a primary care setting. Hospital diagnostic tools are available including an ultrasound device, an ergometer and an electrocardiogram (ECG). All GPs in the region participate in the PC+ intervention and are able to refer non-acute and low-complexity patients with cardiology-related complaints to the PC+ centre. Patients who are already diagnosed with cardiology-related health problems by a cardiologist are not appropriate for PC+ and (if needed) they will be treated by the cardiologist in the hospital-care setting. The consultation at the PC+ centre consists of the following diagnostic tests: a blood test, an ECG, an echo and an exercise test. The diagnostic tests are carried out by multiple health-care professionals, such as nurses, laboratory technicians and physicians, all specialized in cardiology. After the tests the patient meets the cardiologist, who explains the results of the diagnostic tests. The cardiologist sends a comprehensive description of the results of the tests, the diagnosis and his recommendation regarding further treatment (if needed) to the GP. The GP discusses the cardiologist’s recommendation with the patient and based on the principles of shared decision-making the GP and the patient discuss the options for further treatment [24]. Moreover, the GP remains clinically in charge of the patient. The further treatment will depend on the results of the tests and the recommendation of the cardiologist; the three overall options are: 1) the patient needs no care (i.e. the patient has no health problems that need further attention), 2) the patient will remain in the primary care setting (the patient needs low-complexity care, e.g. medication) or, 3) the patient will be referred to secondary care (the patient needs specialist care). The flow of patients is illustrated in Fig. 1.

**Fig. 1 Fig1:**
[figure not shown]
Flowchart: showing the flow of the intervention group and control group

### Care-as-usual: hospital-based outpatient cardiology care

Hospital-based outpatient cardiology care is considered care-as-usual. All GPs are allowed to refer non-acute and low-complexity patients with cardiology-related complaints to the hospital-based outpatient cardiology care. These patients receive the same care as within the PC+ centre, i.e. the same diagnostic tests carried out by health-care professionals with the same level of expertise. After the tests the patient meets the cardiologist, the cardiologist explains the results and they discuss further treatment (if needed). This underlines a significant difference with the intervention: in the PC+ centre the cardiologist provides only a recommendation on further treatment and the GP discusses the options for further treatment (instead of the cardiologist), i.e. within PC+ the GP remains in charge. The flow of patients is illustrated in Fig. 1.

### Study design

The study is a practice-based, quantitative study with a longitudinal observational design, and an additional qualitative study to supplement, interpret and improve the quantitative study. The research study is, at its core, a quantitative study with qualitative data added to provide an added value and deeper, wider and fuller answers to the research questions. These interrelated and reinforcing sub-studies are split up as follows:A quantitative longitudinal observational study aimed at measuring the effects of PC+.A qualitative study to evaluate the process of the introduction of PC+ as well as to amplify, clarify and explain quantitative results.

### Sub-study 1: the quantitative study

#### Aim

The aim of the quantitative part is to measure the effects of the PC+ intervention on the population’s health, patients’ experience of care and health-care costs. To measure the effects the researchers will use the following sources: patient questionnaires, data from the cardiology PC+ centre, data from the regional hospital and health insurance claims data. The data will be collected at four different time points, namely at baseline, before the patient has the first consultation with the cardiologist (T0), a week after the first consultation (T1), 3 months after the first consultation (T2) and 6 months after the first consultation (T3). The outcome parameters, including the dimensions, outcomes, concepts, methods and time frame, are summarized in Table 1.

**Table 1 Tab1:** Overview of the outcome measurements

Dimension	Outcome measure	Concept	Method	Data collection time			
				T0	T1	T2	T3
Population’s health	Health status, health-related quality of life	EQ-5D-5 L	Questionnaires	X	X	X	
		EQ-VAS		X	X	X	
		SF-12		X		X	
Experience of care	Effectiveness	EQ-5D-5 L	Questionnaires	X	X	X	
		Number of referrals	Data^a^	X		X	X
	Timeliness	Time between referral of the GP and appointment at the PC+ centre/hospital	Questionnaires	X	X		
	Patient centred	Questions about the experiences of patients with health care	Questionnaires		X		
	Safety	% Hospital admissions	Data^a^				X
		% Emergency care visits					X
	Equity	Subgroup analysis, e.g. educational level and age	Questionnaires	X		X	
Health-care costs	Health-care costs: primary care, PC+, secondary care and diagnostics	Health insurance claims data	Data^a^				X
	Efficiency	Number of consultations	Data^a^				X
		% Hospital admissions					X
		% Patients referred to hospital after PC+					X

T0 – at baseline: before the consultation

T1 – within a week after the consultation

T2 – 3 months after the consultation (follow-up)

T3 – 6 months after the consultation (follow-up)

^a^Data of the PC+ centre, the hospital and Vektis

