### Data collection

#### Patient questionnaire

All participating patients will be asked to complete questionnaires at three different time points, namely at baseline (e.g. before the consultation with the cardiologist (T0)), within a week after the consultation (T1) and at three-month follow-up after the consultation (T2). The baseline questionnaire (T0) consists of questions about the demographics and health of the patient. Questionnaire 2 (T1) consists of questions about the health of the patient and about the patient’s experience of care. Questionnaire 3 (T2) consists only of questions about the health of the patient. All patients who signed the informed consent, but of whom the researchers did not receive the questionnaire yet, will be kindly reminded to complete the questionnaire. Patients will receive up to two reminders, one by phone and one by a regular mail. Moreover, all outcome parameters are explained in one of the following sections.

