#### Data from the cardiology PC+ centre

Data registered by the PC+ centre include the following information about each patient and their consultation: gender, date of birth, name of referring GP, referral date, reason(s) for referral (including signs and symptoms of the patient), consultation date, name of the treating cardiologist, content of the consultation, recommendation regarding further diagnostics, treatment or referral, added value of the consultation, and whether the patient’s health needs were properly addressed. The starting point is the date of referral to the PC+ centre with a follow-up period of 6 months. All data will be collected by the health-care professionals of the PC+ centre, recorded in one document and exchanged with the researchers.

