#### Data of the regional hospital

Hospital data include two types of patients: 1) control group patients and 2) intervention group patients (patients who have had a consultation at the PC+ centre and are referred to the hospital afterwards). The collected data are similar to the data of the PC+ centre. The starting point of the data collection is the date of referral to the PC+ centre or the hospital-based outpatient cardiology care with a follow-up period of up to 6 months. In addition to the above-mentioned collected patient information, the following hospital data will be provided: the number of consultations, the number of hospital admissions and the number of emergency care visits of a patient over a period of 6 months. The data are extracted from the registration system of the hospital.

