#### Experience of care

The experience of care will be measured using the perspective of the patient, i.e. the patient’s interaction and experience with the health-care system. The outcome parameters are based upon the six dimensions of health-care performance of the IOM: safety, effectiveness, equity, timeliness, patient-centredness and efficiency [19]. As mentioned above, efficiency will be included in the dimension health-care costs.

Effectiveness of care will be measured with the EQ-5D-5 L questionnaire and the percentage of referrals to hospital-based outpatient cardiology care. On the one hand, effectiveness will be measured using the EQ-5D-5 L scores, where it is analysed whether the health of the population is improved after a follow-up of 3 months. On the other hand, effectiveness will be measured using the number of referrals to hospital-based outpatient cardiology care, where it is analysed whether this number is decreased in the period from 2013 to 2017.

Timeliness of care will be examined by measuring the waiting time (in days) between the day the patient is referred by his GP and the day of the first consultation with the cardiologist.

Patient-centred care will be measured using items based on the Consumer Quality (CQ) index. The CQ index is a standardized method for measuring experiences of patients with health care [38]. The questionnaire (T1) includes 30 questions about the experiences of the patients with health care, with specific regard to their experiences with the health-care professionals (e.g. *‘Did you feel welcome and at ease?’* and *‘Did the health-care professionals listen attentively?’*).

Safety of care will be measured using data that will be made available by the hospital concerning: 1) hospital admissions; 2) emergency care visits.

Equity of care will be examined by performing subgroup analysis on all outcome measures regarding educational level (high versus low) and age (lower than median and higher than median).

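### Waiting time is sourced from questionnaires although the study already registers the dates that define it, explicitly for PC+ patients and probably for controls

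*Protocol article*

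**What the plan says.** In Table 1 of the protocol article, the Timeliness row reads "Time between referral of the GP and appointment at the PC+ centre/hospital". Its method is questionnaires, with crosses at T0 (before the consultation) and T1 (within a week after it).

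The Experience of care section gives the definition: "Timeliness of care will be examined by measuring the waiting time (in days) between the day the patient is referred by his GP". The interval ends when the patient first sees the cardiologist. The section names no data source.

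The section on data from the PC+ centre opens its list with "Data registered by the PC+ centre include the following information about each patient and their consultation", and the list includes "referral date, reason(s) for referral (including signs and symptoms of the patient), consultation date". The section on hospital data says "The collected data are similar to the data of the PC+ centre" and adds "The starting point of the data collection is the date of referral to the PC+ centre or the hospital-based outpatient cardiology care".

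The Patient questionnaire section describes the first form thus: "The baseline questionnaire (T0) consists of questions about the demographics and health of the patient". The T1 form covers health and experience of care. Patients who have consented but not returned a form get up to two reminders. The missing-data section assigns multiple imputation to missing values of non-repeated measures.

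**The concern.** Waiting time in days is a difference between two recorded events, not a perception. Table 1 takes other recorded events (referrals, admissions, emergency visits, consultations) from PC+ centre, hospital or Vektis data. Timeliness is the exception, and no reason is given.

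The choice has two consequences. A patient who does not return the relevant form has no observed value, although the study may hold both dates for that patient. Any patient-reported value also comes from someone who knows which route was taken and who, under Study population, took part in choosing it. Reporting error could therefore differ between groups, and a propensity score built on baseline characteristics does not correct for that.

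Timeliness is also one of the dimensions that the objectives section expects PC+ to improve, through shorter waiting. The comparison should rest on the best data the study has.

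**Working it through.** **1. Are the two dates available?**

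| Item | Intervention group | Control group |
|---|---|---|
| Referral date | Listed in the PC+ centre data | Needed as the starting point of the hospital and claims data; content described as similar |
| First-consultation date | Listed in the PC+ centre data | Inferred from the word similar |
| Coverage | Stated for each patient | Not stated |
| Capture | Recorded by the centre's professionals in one document | Extracted from the hospital's registration system |

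Availability is explicit for PC+ patients and a reasonable inference for controls.

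**2. Does the questionnaire route fit the outcome?** T0 precedes the consultation, so the completed interval cannot be observed then. The two crosses make sense if T0 supplies the start of the interval and T1 the end. On that reading a patient needs both forms to have a value. The short description of the T0 form mentions no such item, but an article need not list every question.

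**3. What could non-response cost?** The article gives no figure for waiting time. Its only loss figure is the 20% dropout allowance in the sample-size section.

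- Reproducing the plan's figure: (1.96 + 0.84)² × 0.09 × 0.91 × 2 / 0.06² = 356.7, so 357 per group against the stated 358. Then 357 × 1.2 = 428.4, which rounds up to the stated 429. This calculation concerns referral proportions, not waiting time. I use only the 429 and the 20%.
- Assumption: a fraction L of patients lacks a questionnaire value, registered dates are complete, and imputation recovers nothing. The standard error is proportional to 1/√n, so registered dates reduce it by 1 − √(1 − L).
- L = 0: no reduction.
- L = 10%: 1 − √0.90 = 0.051, about 5%.
- L = 20%: 429 × 0.8 = 343 per group, and 1 − √(343/429) = 0.106, about 11%.
- On the same assumptions, the difference detectable with 80% power (two-sided 0.05) is 2.80 × √(2/n) standard deviations. That is 0.191 SD with 429 per group and 0.214 SD with 343.

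**4. Reporting error.** Neither its size nor the questionnaire wording is given. Independent error with standard deviation f times the true one multiplies the variance by 1 + f². With 343 per group and a true difference of 0.191 SD, power is about 71% for f = 0, 68% for f = 0.25, 61% for f = 0.5 and 43% for f = 1. These values of f are assumed, so the figures show the direction of the effect and do not estimate it.

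**The case against.** The case for leaving the plan alone has real substance.

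- **Both dates for every patient.** A reader might infer this for both groups. Only the PC+ list states it; for controls it is inferred. This stands.
- **Comparability.** The registrations are two capture routes, one per group, and nothing says that the hospital's referral date is the day the GP referred. A common questionnaire could be the more uniform instrument. This stands as a condition on the fix.
- **Recall.** No wording shows that patients are asked to recall dates, and each form could capture one end of the interval close to the event. This stands: reporting error is possible, not demonstrated.
- **Model misfit.** A reader might infer from the two crosses that waiting time is a repeated measure to be forced into the group-by-time model. The documents do not support this. The crosses may mark the two ends of one interval, the missing-data section recognises non-repeated measures, and an article may leave the model for a single-value outcome to a fuller plan.
- **Simple loss of non-responders.** This cannot be inferred either. Reminders and multiple imputation are planned.
- **The 20%.** It is a general dropout allowance in a study followed for 3 to 6 months. Loss by one week may be smaller.
- **Patient perspective.** Experience of care is said to be measured from the patient's viewpoint. Yet Table 1 already takes referrals and safety, in the same dimension, from records, and the definition in days is not a perception.

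These points limit the size of the concern. They give no reason to prefer a patient-reported or imputed value to a registered one, once the fields are shown to be comparable.

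**Conclusion.** The concern holds as a cheap, worthwhile improvement. The article fixes a weaker source for an objective outcome while describing a better one, explicit for PC+ patients and probable for controls.

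The size is modest and not given in the document. The upper figure of about 11% in the standard error requires that all of the 20% dropout is questionnaire loss, that registered dates are complete in both groups, and that imputation recovers nothing. With less loss, or useful imputation, the gain is smaller. Removing any reporting error would add to it by an unknown amount. The sample size is unaffected, since it rests on referral proportions.

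It would go too far to conclude that the timeliness comparison is biased. The documents establish neither a reporting error nor a direction for one.

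**What to change.** 1. In Table 1 and in the Experience of care section, define waiting time as registered first-consultation date minus registered GP-referral date, in both groups. Change the Table 1 method from questionnaires to PC+ centre and hospital data.
2. First confirm that the hospital extract holds both dates, that its referral field records the GP's referral day in the same way as the PC+ field, and that both fields are adequately complete.
3. Compare the value once per patient, adjusted for the propensity score.
4. Keep any questionnaire item as perceived waiting time or as a check on the registered dates.

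The cost is a wording change in two places and the comparability check on the date fields. If the hospital extract is as similar as described, no new data collection is needed. If the check fails, the article should say so and give that as the reason for keeping the questionnaire.

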### Study population

The study population consists of adult patients (≥18 years) with non-acute and low-complexity cardiology-related health complaints, registered with a GP in the region of the pioneer site. Based on the principles of shared decision-making the GP and the patient will discuss the options for referral which will be either the PC+ centre (intervention group) or the hospital-based outpatient cardiology care (control group). The decision will be based on expertise and experience of the GP, the severity of the complaints of the patient and the preferences of the patient. Less sever, non-acute and low-complex patients should be referred to PC+. At the moment, no specific criteria are included for the referral to PC+. The GP is in charge of referring a patient to the PC+ centre or the hospital-based outpatient cardiology care, i.e. the researchers do not have any influence on the referrals.

Excluded from participation are patients who are already diagnosed with cardiology-related health problems by a cardiologist and patients who have received balloon angioplasty or bypass surgery in the past 18 months. Furthermore, patients with acute health problems who require immediate hospital care and/or patients arriving at the emergency department of the hospital are excluded from participation.

### Recruitment of patients

Regarding the allocation of patients, this is a practice-based study and therefore the allocation of patients is not random but based on the decision of the GPs. The patient enrolment of both the intervention group and the control group starts when a GP refers a patient to PC+ or hospital-based outpatient cardiology care. Furthermore, it will be statistically tested whether the groups differ in patients’ characteristics at baseline. In case the there is a difference in patients’ characteristics at baseline, the propensity score method (PSM) is used to statistical control for the differences [25]. In addition, the GP will inform all patients about the study. Before the consultation at the PC+ centre or the hospital the patients will receive an information letter with an informed consent form. In this letter they are asked if they would like to participate in the study. All eligible patients have to give informed consent. The flow of participants and the time of measurements, i.e. data collection, are summarized in Fig. 2.

**Fig. 2 Fig2:**
[figure not shown]
Flowchart: flow of the participants and measurements

### Data collection

#### Patient questionnaire

All participating patients will be asked to complete questionnaires at three different time points, namely at baseline (e.g. before the consultation with the cardiologist (T0)), within a week after the consultation (T1) and at three-month follow-up after the consultation (T2). The baseline questionnaire (T0) consists of questions about the demographics and health of the patient. Questionnaire 2 (T1) consists of questions about the health of the patient and about the patient’s experience of care. Questionnaire 3 (T2) consists only of questions about the health of the patient. All patients who signed the informed consent, but of whom the researchers did not receive the questionnaire yet, will be kindly reminded to complete the questionnaire. Patients will receive up to two reminders, one by phone and one by a regular mail. Moreover, all outcome parameters are explained in one of the following sections.

#### Data from the cardiology PC+ centre

Data registered by the PC+ centre include the following information about each patient and their consultation: gender, date of birth, name of referring GP, referral date, reason(s) for referral (including signs and symptoms of the patient), consultation date, name of the treating cardiologist, content of the consultation, recommendation regarding further diagnostics, treatment or referral, added value of the consultation, and whether the patient’s health needs were properly addressed. The starting point is the date of referral to the PC+ centre with a follow-up period of 6 months. All data will be collected by the health-care professionals of the PC+ centre, recorded in one document and exchanged with the researchers.

#### Data of the regional hospital

Hospital data include two types of patients: 1) control group patients and 2) intervention group patients (patients who have had a consultation at the PC+ centre and are referred to the hospital afterwards). The collected data are similar to the data of the PC+ centre. The starting point of the data collection is the date of referral to the PC+ centre or the hospital-based outpatient cardiology care with a follow-up period of up to 6 months. In addition to the above-mentioned collected patient information, the following hospital data will be provided: the number of consultations, the number of hospital admissions and the number of emergency care visits of a patient over a period of 6 months. The data are extracted from the registration system of the hospital.

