Finally, it is supposed that the introduction of PC+ will lead to reduced health-care costs by: 1) fewer referrals to hospital-based outpatient care because of the introduction of PC+, 2) lower costs in PC+ than in hospital-based outpatient care, due to lower overhead costs (i.e. the same cardiology screening will costs less in PC+), 3) less use of additional hospital-based services because it is supposed that a significant number of the patients referred to PC+ will not be referred to hospital care afterwards, but will remain in the primary care setting, and 4) GPs will gain more knowledge because of the enhanced collaboration and communication with the cardiologists. Hence, in the long term, it is possible that they will refer fewer patients, to either PC+ or hospital-outpatient care, for a cardiology screening and instead treat the patients themselves.

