#### Health insurance claims data

This study will only focus on the health-care costs of patients, which will be measured using the health insurance claims data of the participants, which are available at Vektis. Vektis is a national information centre for all the health insurance companies in the Netherlands. The centre collects all data on the health-care utilization and health-care costs of all Dutch residents [26]. Health insurance claims data will be used to examine whether the health-care costs of an intervention patient (PC+) is different to the health-care costs of a control patient. To compare the health-care costs of an intervention patient with that of a control patient, the health insurance claims of each patient participating in the intervention or control group will be used, with a focus on GP care, PC+ and hospital care. Moreover, it has been decided to take into account the health-care costs per participant over a period of 6 months. The starting point is the date of referral to the PC+ centre (intervention group) or the hospital-based outpatient cardiology care (control group).

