#### Health-care costs

Health-care costs will be measured using health insurance claims data. This study will not cover all related health-care costs but will only focus on health-care costs (including patients’ compulsory deductible). Out-of-pocket payments and indirect costs made from a societal perspective (e.g. labour market, informal care) will not be included. The health-care costs per participant is measured over a period of 6 months after the consultation at the PC+ centre or the hospital-based outpatient cardiology care. This concerns data regarding health-care costs on primary care, PC+, hospital care and diagnostics.

Efficiency of care means, according to the IOM, avoiding waste, particularly waste of equipment, supplies, ideas and energy [19]. With regard to this research, it will be measured whether the number of consultations of patients, hospital admissions and referrals will decrease after the implementation of PC+, which is related to efficient use of equipment and health-care professionals and time of patients. Efficiency of care will be measured using data from the cardiology PC+ centre, the hospital and Vektis. The data will consist of the following items: 1) the average number of consultations at the hospital of a patient over a period of 6 months; 2) the average number of hospital admissions of a patient over a period of 6 months; and 3) the number and percentage of patients that are referred to hospital care after PC+.

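### The hospital extract takes all control patients but only PC+ patients later referred to hospital, so the named safety source omits emergency events in PC+ patients never referred on

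*Protocol article*

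**What the plan says.** **Who is in the hospital extract.** Under Data of the regional hospital, the protocol article states "Hospital data include two types of patients: 1) control group patients" and then, as the second type, "intervention group patients (patients who have had a consultation at the PC+ centre and are referred to the hospital afterwards". Besides items similar to the PC+ centre's own data, this source supplies consultations together with "the number of hospital admissions and the number of emergency care visits of a patient over a period of 6 months".

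**Which source serves safety.** Under Experience of care: "Safety of care will be measured using data that will be made available by the hospital concerning: 1) hospital admissions; 2) emergency care visits". No other source is named in that sentence.

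**Which other sources appear.** The footnote to Table 1 applies one description to every row marked as data, the safety rows included: "Data of the PC+ centre, the hospital and Vektis". Under Health-care costs, the efficiency items, which include admissions, have the same three sources: "Efficiency of care will be measured using data from the cardiology PC+ centre, the hospital and Vektis". Under Health insurance claims data, coverage is complete: "the health insurance claims of each patient participating in the intervention or control group will be used". The purpose stated there is to compare costs between the groups.

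**How large the uncovered group may be.** The section on objectives and premises expects that "a significant number of the patients referred to PC+ will not be referred to hospital care afterwards". It gives no percentage.

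**The concern.** A control patient enters the hospital extract because of group membership. A PC+ patient enters it only after a later event, the onward referral. The PC+ patient whose outcome matters most for safety is one judged not to need hospital care who then presents as an emergency. On the stated rule that patient is not in the extract.

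The protocol supposes that PC+ leaves safety unchanged. If events are counted fully in one group and selectively in the other, an apparent finding of equal or better safety could come from the data rule and not from the care. The study could then neither support nor refute its own safety premise.

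**Working it through.** **Step 1. Which PC+ patients and events are uncovered.** The intervention section gives three routes after the PC+ consultation: no further care, staying in primary care, or referral to secondary care. The hospital extract names only patients on the third route. The list of data held by the PC+ centre contains neither admissions nor emergency visits, so it does not fill the gap. The Background says that hospital care requires a GP referral except in an emergency. A planned admission would thus normally follow a referral, and a referral made some time after the PC+ consultation can still fall within the wording. What remains outside is the emergency visit, and any admission arising from it, in a PC+ patient never referred on.

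**Step 2. Direction.** The documents give no figure for the following, so all are assumptions:
- *R*: true 6-month event risk, taken as equal in both groups
- *f*: share of PC+ patients referred on
- *g*: share of PC+ events that occur in referred patients and so are captured
- *k*: risk in referred relative to non-referred patients

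If all PC+ patients are in the denominator, the observed PC+ risk is R × g and the apparent risk ratio is g. This is below 1 whenever any event is missed.

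If only referred PC+ patients are counted, the observed PC+ risk is R × g / f and the apparent risk ratio is g / f. With f = 0.4 and g = 0.8 this is 2.0, against PC+. With f = 0.6 and g = 0.5 it is 0.83.

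**Step 3. Range of g.** g = kf / (kf + 1 − f).
- k = 1: g = f, so f = 0.2 to 0.5 gives g = 0.2 to 0.5.
- k = 4: f = 0.2 gives 0.8 / 1.6 = 0.5, and f = 0.5 gives 2.0 / 2.5 = 0.8.

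**Step 4. Illustrated effect, all PC+ patients in the denominator.** The group size is the protocol's 358 per group before dropout. The chance of a falsely significant advantage for PC+ is Φ((Δ − 1.96 × SE0) / SE1), where SE0 is the pooled and SE1 the unpooled standard error of the difference. For R = 5% and g = 0.5: Δ = 0.025, SE0 = √(2 × 0.0375 × 0.9625 / 358) = 0.0142, SE1 = √((0.05 × 0.95 + 0.025 × 0.975) / 358) = 0.0142, which gives about 42%.

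| True risk R | g = 0.8 | g = 0.5 | g = 0.2 |
|---|---|---|---|
| 2% | 1.6% observed; 6% | 1.0%; 20% | 0.4%; 50% |
| 5% | 4.0%; 9% | 2.5%; 42% | 1.0%; 88% |
| 10% | 8.0%; 15% | 5.0%; 72% | 2.0%; 99.5% |

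Each cell gives the observed PC+ risk, then the chance of a falsely significant result favouring PC+.

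**Step 5. Masking of harm.** With a true risk ratio T, the observed ratio is T × g. A true excess of up to 1 / g would read as no difference or better: 1.25 at g = 0.8, and 2.0 at g = 0.5.

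**Step 6. With equal ascertainment.** If the extract covered every PC+ participant, g = 1, and the apparent ratio under equal true risk would be 1.0.

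**The case against.** The strongest reply is that a source covering everyone is already in the plan. Claims data exist for each participant, the Table 1 footnote lists them for the data rows including safety, and the efficiency paragraph lists them for admissions. This largely stands for efficiency: a reader might infer that admissions are biased there too, but the text does not support saying so with confidence. It does not settle safety. The footnote does not say which source serves which row, the safety sentence names the hospital alone, and the claims section describes a cost comparison. Nowhere are claims said to supply emergency visits or admissions for non-referred PC+ patients. Taking events from hospital records in one group and claims in the other would itself be unequal ascertainment.

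Second, referral gatekeeping makes the gap smaller than it first looks. This stands. A reader might infer that all hospital events in PC+ patients sent back to the GP are lost; Step 1 shows that the loss is confined mainly to emergency presentations.

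Third, the parenthesis may merely explain why PC+ patients appear in hospital records, and the full extraction specification is not shown. That is possible. However, the qualitative sub-study's population section uses nearly the same description for a subgroup listed separately from PC+ patients in general, which favours reading it as a restriction.

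Two further inferences go too far. The bias does not always favour PC+, because its direction depends on the denominator. Nor does the rule alter the intention-to-treat groups: assignment is untouched, and the fault lies in how events are found.

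**Conclusion.** The point holds for safety. As written, the only source named in the safety paragraph covers all control patients and a selected part of the PC+ group, so emergency visits and resulting admissions in PC+ patients never referred on are outside it. With every PC+ participant in the denominator the comparison is tilted towards PC+; with only referred patients counted it can be tilted against PC+. Neither comparison is interpretable as a test of equal safety.

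For admissions as an efficiency outcome the loss is possible but not established.

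The size cannot be derived from the documents. The tabulated figures rest wholly on assumed event rates and capture shares, on equal true risk in the two groups, and on no recovery of events from claims. Given the referral gatekeeping, the low-capture column (g = 0.2) would require most PC+ events to be emergencies in never-referred patients, and should be read as an extreme.

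**What to change.** Rewrite the hospital data section so that admissions, emergency visits and consultations over the 6 months are extracted for all consenting participants in both groups, whether or not a PC+ patient was later referred. Alternatively, state that these events come from the Vektis claims, applied identically to both groups. If hospital records are used, the claims can serve as a cross-check.

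State that all PC+ participants form the denominator for the safety and admission outcomes. Then reconcile four places so that each outcome has one named source: the Table 1 footnote, Data of the regional hospital, the safety sentence under Experience of care, and the efficiency paragraph under Health-care costs.

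The cost is a wider query against the list of consenting participants. The region has one hospital and claims are already requested for every participant, so no new patients, visits or questionnaires are needed.
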